## Abbreviations

|        |                                                                                                                                                        |
|--------|--------------------------------------------------------------------------------------------------------------------------------------------------------|
| AED    | Academy of Educational Development                                                                                                                     |
| AGP    | Acid glycoprotein                                                                                                                                      |
| Aids   | Acquired immune deficiency syndrome                                                                                                                    |
| ARI    | Acute Respiratory Infection                                                                                                                            |
| CRP    | C-reactive protein                                                                                                                                     |
| EU     | European Union                                                                                                                                         |
| FAO    | Food and Agriculture Organization of the United Nations                                                                                                |
| Fe     | Iron                                                                                                                                                   |
| FFP    | Food Facility Project                                                                                                                                  |
| FSTP   | Food Security Thematic Program                                                                                                                         |
| GIZ    | German Society for International Cooperation                                                                                                           |
| HAZ    | Height for Age z-Score                                                                                                                                 |
| HH     | Households                                                                                                                                             |
| HIV    | Human Immunodeficiency Virus                                                                                                                           |
| IMCF   | Improving the dietary intakes and nutritional status of infants and young children through improved food security and complementary feeding counseling |
| IRB    | Institutional Review Board                                                                                                                             |
| MAFF   | Ministry of Agriculture, Forestry and Fisheries                                                                                                        |
| MALIS  | Improving Food Security and Market Linkages for Smallholders project                                                                                   |
| MDG    | Millennium Development Goals                                                                                                                           |
| MTCT   | Mother-to-Child Transmission                                                                                                                           |
| NCHS   | National Center for Health Statistics (US)                                                                                                             |
| NGO    | Non-governmental organizations                                                                                                                         |
| RBP    | Retinol Binding Protein                                                                                                                                |
| RDA    | Recommended Dietary Allowances                                                                                                                         |
| SMART  | Standardized Monitoring and Assessment of Relief and Transitions                                                                                       |
| SUN    | Scaling up nutrition                                                                                                                                   |
| TAC    | Technical Advisory Committee                                                                                                                           |
| TfR    | Transferrin Receptor                                                                                                                                   |
| TIPs   | Trials of Improved Practices                                                                                                                           |
| UNICEF | United Nations International Children's Emergency Fund                                                                                                 |

|       |                                                    |
|-------|----------------------------------------------------|
| USAID | United States Agency for International Development |
| Vit A | Vitamin A                                          |
| WAZ   | Weight for Age z-Score                             |
| WHO   | World Health Organisation                          |

## **1 Abstract**

Undernutrition remains one of the biggest challenges in developing countries. Children aged 0-23 months are the most vulnerable group with a peak incidence of mortality and morbidity. The Cambodian Demographic and Health Survey 2010 estimated a national stunting prevalence of 40%. Results show that stunting increases after six months of age when most children receive complementary feeding. The promotion of a nutrient-dense diet based on locally available foods is essential to improve the nutritional status of young children. In order to optimize infants and young children's diets, the FAO project "Improving food security and Market Linkages for Smallholders in Otdar Meanchey and Preah Vihear Provinces (MALIS)" will implement a food security project with a nutrition education component.

The objective of the research is to evaluate the effectiveness of the behavior change messages which will be delivered through a community based intervention involving community based organizations. The research design encompasses both qualitative and quantitative methods, including two cross-sectional surveys, focus group discussions and key informant interviews. The first cross-sectional survey will take place prior to the intervention to assess the baseline nutrition security situation of families with children below two years in the MALIS project region. The behavior change communication strategies will be implemented in the prior selected intervention areas by the MALIS project. The second cross-sectional survey will be conducted after at least 18 months of intervention evaluating the impact of the intervention by a research team.

The primary outcome parameter to be measured will be mean Height for Age z-Scores (HAZ). Secondary outcome parameters will be vitamin A deficiency, iron deficiency and behavior change. Methods for data collection will include anthropometric measurements, questionnaires, collection of blood plasma by finger prick and focus group discussions. Statistical analysis will compare primarily the difference of the mean height-for-age z-score of children in intervention and control areas.

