## 4 Hypothesis

Assuming that behavior change messages on breastfeeding and complementary feeding practices as well as hygiene aspects as generated by the TIPs are widely accepted and out into practice by the mothers with children ages 0-23 months the data assessment will be based on the following hypotheses:

1. The Height for age Z-Score (HAZ) of children below 2 years will increase if TIPs recommendations and recipes are locally available and accepted. At conclusion of the intervention, there will be a difference of 15% of the HAZ between interventions and controls:

$$H0: \mu \text{ HAZ (intervention)} = \mu \text{ HAZ (control)}$$

$$H1: \mu \text{ HAZ (intervention)} > \mu \text{ HAZ (control)}$$

2. Secondly, prevalence of anemia, vitamin A deficiency as well as morbidity rates will be reduced:

a) Anemia (A) among children between 6 and 23 months, defined as hemoglobin level of < 11g/dl, will decrease by 25 %:

$$H0: P(A| \text{intervention}) = P(A| \text{control}),$$

$$H1: P(A| \text{intervention}) < P(A| \text{control})$$

b) Retinol binding protein (RBP) levels will decrease by 15% among children with a C-reactive protein (CRP) level of < 12mg/l:

$$H0: \mu \text{ RBP (intervention)} = \mu \text{ RBP (control)},$$

$$H1: \mu \text{ RBP (intervention)} < \mu \text{ RBP (control)}$$

c) Prevalence of children with presumed acute respiratory infections and fever (ARI) and diarrhea (D) in the last two weeks prior the survey will decrease by 25%:

$$H0: P(ARI| \text{intervention}) = P(ARI| \text{control}),$$

$$H1: P(ARI| \text{intervention}) < P(ARI| \text{control})$$

$$H0: P(D| \text{intervention}) = P(D| \text{control}),$$

$$H1: P(D| \text{intervention}) < P(D| \text{control})$$

d) There will be differences in knowledge of age-appropriate complementary feeding (KCF) of children between caretakers measured using a knowledge score in interventions and controls.

H0:  $\mu$  KCF (intervention) =  $\mu$  KCF (control),

H1:  $\mu$  KCF (intervention) >  $\mu$  KCF (control).

e) TIPs formative research generates nutritionally improved, culturally acceptable and affordable recipes which result in improved feeding practices and food intake which will result in a higher dietary diversity score for the children.

There will be differences in dietary diversity (DD) between interventions and controls:

H0:  $\mu$  DD (intervention) =  $\mu$  DD (control),

H1:  $\mu$  DD (intervention) >  $\mu$  DD (control).

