## 6.4 Sample size for baseline and impact survey

The appropriate sample size for the cross-sectional baseline survey will be determined largely by three factors (52):

- a) estimated prevalence of the variable of interest,
- b) desired level of confidence, and
- c) acceptable level of error.

Using ENA for Smart sample size calculator (49) and considering a population size of 15000 children under two in the surveyed area, 50% of stunting (key indicator), desired precision of +/- 5% and a design effect of 3 the sample size calculation results in 1124 children. Avillage is the cluster unit.

The cross-sectional impact survey sample size will be based on the formula proposed by Haynes and Moulton for cluster randomized trials Haynes and Moulton (50):

$$n = (z_{\alpha/2} + z_{\beta})^2 \frac{(\sigma_0^2 + \sigma_1^2)}{(\mu_0 - \mu_1)^2}$$

The sample size calculation resulted in 335 children for each treatment arm, considering a power of 80%, confidence level of 95%,  $\sigma_0 = 1.5$  and  $\sigma_1 = 1.2$  and estimated 15% increase of HAZ ( $\mu_0 = -1.96$ ,  $\mu_1 = -1.66$ ).

Nevertheless, to adjust for intra-class correlation (ICC), a design-effect should be included. The design effect (DEFF) is defined as:

---

Values have been estimated from the available literature.

$$DEFF = 1 + ICC (m-1)$$

Considering that  $m=19$  children per cluster (village) will be measured, and an estimated ICC of 0.03 is applied (see annex 10.3), the  $DEFF= 1 + 0.03*18=1.54$ . Multiplying the DEFF-value with the above calculation this results in 516 children below two for each treatment arm. Adding an extra 10% to account for drop-outs or non-responders results in a sample size of 568 children below two years for each treatment arm.

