## 6.5 Randomization procedure

A simple randomization proportional to population per district will be conducted to select 75 survey villages for the baseline. In each village 15 households with children under two will be randomly selected. In case there are less than 15 households with children under two in the selected village, the missing number of households will be randomly selected from the closest neighbouring village. The intervention and control villages are assigned following a restricted randomization based on the results of the baseline survey.

This implies that randomization will take place after adjusting for certain variables that might interfere with variables of interest to the study. Variables of adjustment are:

- district officer
- level of stunting
- total village population
- average land holding size
- wealth status
- access to health posts, nutrition rehabilitation unit, or nutrition counseling by a NGO

The selected clusters will be the objective of randomization. Randomization will be done using the Software package “Experiment” and the operation “randomize”. The “Experiment”-package is a software extension to the statistical software  $R^{\circledast}$ . It serves to design and analyze different types of randomized trials, including cluster randomized trials, block, or matched pair designed trials (60). The baseline and the impact survey will randomly select the study participants in the selected clusters.

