## **6.6 Statistical methods and analysis**

Data assessment and data analysis will follow the adopted UNICEF framework of underlying causes of malnutrition and mortality (see Chapter 3.1). Nutritional status will be interpreted as a result of household food security, i.e. access to food and food availability, adequate social and care environment, i.e. direct caring behaviors, women's role, status and rights, social organizations and networks, and functioning public health system, i.e. health environment and access to health.

The cross sectional surveys will be used to gather information of the above mentioned parameters before and after the intervention. The data will be entered into the SPSS editor (IBM SPSS Statistics version 20) and checked for inconsistencies by two individuals independently. Flagged values will be checked based on the filled questionnaires and if applicable the study participants will be approached to verify the result.

Statistical analysis will be performed using the statistical packages of IBM SPSS statistics (version 20). At first the variables will be tested for normal distribution, followed by a descriptive analysis of prevalence of malnutrition, anemia, vit-A deficiency, respiratory infections and fever (ARI), diarrhea, morbidity rates, dietary diversity, and knowledge of age appropriate feeding. The latter involves a development of a score to describe the knowledge about age appropriate feeding. Further, regression analysis will be applied looking for causalities of malnutrition in the studied area.

Focus group discussions will be based on a general interview guide approach. The interview guide will include subjects of implementation, acceptance and obstacles of TIPs. They will be analyzed by applying the content analysis according to Mayring (51) and facilitated by the use of MAXQDA©-software (53).

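### The design and sample size account for village clustering, but the stated primary HAZ comparison and section 6.6 do not carry it, the restriction variables, baseline or child age into the analysis

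*Protocol*

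**What the plan says.** **Design.** Protocol 6.4 names the village as the cluster unit and sizes the impact survey with a formula for cluster randomised trials, an ICC of 0.03, 19 children per village and a design effect of 1.54. Section 6.5 randomises the selected clusters, and says that "randomization will take place after adjusting for certain variables that might interfere with variables of interest to the study". Six such variables are listed, among them level of stunting, village population and wealth status.

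**Primary comparison.** The Abstract states: "Statistical analysis will compare primarily the difference of the mean height-for-age z-score of children in intervention and control areas". Section 4 sets it out as a comparison of two means: "At conclusion of the intervention, there will be a difference of 15% of the HAZ between interventions and controls".

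**Analysis section.** Section 6.6 names SPSS version 20 and then a sequence of steps: "At first the variables will be tested for normal distribution, followed by a descriptive analysis of prevalence of malnutrition", with other descriptive outcomes following. It ends the quantitative part with: "Further, regression analysis will be applied looking for causalities of malnutrition in the studied area". No test or model is named for the contrast between arms. Village, cluster, restriction variables, baseline values and child age are not mentioned as parts of that contrast.

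**The concern.** A trial that allocates villages has to be analysed with villages as the unit of allocation, either through a random village effect or on village summaries. The protocol follows this logic up to the sample size and then stops. The only written primary contrast is between the means of children in two sets of areas, and the only regression in 6.6 has another purpose, the search for causes of malnutrition. An analyst who followed the text literally could run a two-sample test on children in SPSS. That would understate the standard error and make the confidence interval for the primary outcome too narrow.

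A second, smaller matter is precision. Child age is recorded for every child (6.8.3), and a baseline survey provides village means before allocation. Table 1 shows stunting rising from 10.4% below 6 months to 46.7% at 18-23 months, so HAZ varies with age even though it is age-referenced. Neither source is used in the stated comparison.

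**Working it through.** **1. Reproduce the plan's sample size.** Inputs from 6.4: "considering a power of 80%, confidence level of 95" per cent, standard deviations 1.5 and 1.2, and an "estimated 15% increase of HAZ".

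- Formula: n = (1.960 + 0.842)² × (1.5² + 1.2²) / δ², with 1.5² + 1.2² = 3.69.
- With δ = 0.15 × 1.96 = 0.294: n = 335.1. This agrees with the plan: "The sample size calculation resulted in 335 children for each treatment arm". The printed means, -1.96 and -1.66, differ by 0.30 and would give 322, so the plan used the unrounded 0.294.
- Design effect: 1 + 0.03 × 18 = 1.54; 335 × 1.54 = 515.9, so 516.
- Adding 10%: 516 × 1.10 = 567.6, so 568.

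All three figures reproduce. About 181 children per arm (516 - 335) are added for clustering.

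**2. Type I error if clustering were ignored.** A child-level test understates the variance by the design effect, so its true two-sided error is 2 × [1 - Φ(1.96/√DEFF)].

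| ICC (m = 19) | DEFF | 1.96/√DEFF | True error |
|---|---|---|---|
| 0.01 (assumed) | 1.18 | 1.804 | 7.1% |
| **0.03 (protocol)** | **1.54** | **1.579** | **11.4%** |
| 0.10 (assumed) | 2.80 | 1.171 | 24.2% |

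A simulation with 27 villages per arm, 19 children each and ICC 0.03 (40,000 runs) gave 11.4% for the child-level t-test and 5.1% for a t-test on village means.

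**3. Power when clustering is respected.** At 516 per arm the standard error is √(3.69 × 1.54/516) = 0.1049. Then 0.294/0.1049 = 2.80 and Φ(2.80 - 1.96) = 80%. At 568 per arm the same calculation gives 83.6%. The planned number therefore already pays for a clustered analysis without covariates. In the simulation the village-means test had 78% power with 27 villages per arm.

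**4. What adjustment could add (516 per arm, ICC 0.03, m = 19).** As a share of total variance, a village mean has variance 0.03 + 0.97/19 = 0.0811.

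- *Child age.* Converting the Table 1 stunting prevalences for the five bands below 24 months into band means, assuming normal HAZ with equal SD in each band, gives a between-band share of about 15%. Applied to the within-village part: reduction = 0.97 × 0.15/19 / 0.0811 = 9.4%. Power = Φ(2.80/√0.906 - 1.96) = 84%. For an assumed share of 5% to 20%, power is 81% to 85%.
- *Baseline village mean HAZ.* With 15 children per village (6.5), reliability = 15 × 0.03/(1 + 14 × 0.03) = 0.32. With an assumed village correlation over time of 0.8: reduction = 0.8² × 0.03 × 0.317/0.0811 = 7.5%. Power = Φ(2.80/√0.925 - 1.96) = 83%. For a correlation of 0.5 to 1.0, power is 81% to 85%.
- *Both.* Reduction = 9.4% + 7.5% = 17.0% before rounding. Power = Φ(2.80/√0.830 - 1.96) = 87%. The corners of the two ranges give 82% (reduction 6.1%) and 90% (reduction 24.3%).

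**The case against.** The strongest reply is that silence is not a wrong choice. The sentence in the Abstract names a contrast, and a mixed model or a test on village means estimates the same contrast. Sections 6.4 and 6.5 plainly recognise clustering, and a statistical analysis plan that is not at hand may name the model. This stands in part. A reader might infer that the protocol commits to a raw child-level test and that its error rate is therefore wrong. The documents do not support that: no unit of analysis or test is named, so the 11% is conditional on how the comparison is run. What remains is that 6.6 does set out an analysis path, with software, normality tests, descriptive steps and a regression, and that path leaves out the feature on which 6.4 and 6.5 are built.

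The reply is also right about covariates. Leaving out age or baseline does not bias a randomised contrast or inflate its error rate, and ignoring balanced restriction variables tends to make a test conservative. Baseline stunting already enters through the allocation. Nor is the trial underpowered for want of adjustment, since 516 per arm gives 80% without it.

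Two further readings do not hold. The design effect of 3 in 6.4 belongs to the baseline prevalence survey and should not be used to project the error of the between-arm HAZ test. And nothing in 6.6 makes the normality check decide the primary test, or presents the regression on causes as the primary analysis, so neither has to be removed.

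Finally, 6.5 fills shortfalls from the closest neighbouring village, so some baseline village means may mix villages. That would weaken the gain from baseline adjustment.

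**Conclusion.** The point holds as a gap between the design and the stated analysis. Villages are randomised under restriction and the sample is inflated by 1.54, but the primary comparison as written, and section 6.6, do not carry clustering, the restriction variables, baseline or age through.

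The consequence for validity is conditional. An ordinary child-level test would have a two-sided type I error of about 11% at the protocol's ICC of 0.03 and 19 children per village, more than twice the nominal 5%. This figure uses only the protocol's inputs for the impact survey.

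The consequence for precision is a forgone gain of about 3 to 7 power points at 516 per arm: 80% to about 84% with age, 83% with baseline village mean and 87% with both. These rest on three assumptions: age explains 15% of within-village variance, the village correlation over time is 0.8, and the ICC is 0.03.

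**What to change.** In 6.6, name the primary analysis of HAZ at the impact survey:

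- a linear mixed model with a random village effect and arm as fixed effect, or an equivalent analysis of village summaries;
- prespecified adjustment for child age, baseline village mean HAZ and the variables used in the restricted randomisation;
- a two-sided 95% confidence interval, which matches the two-sided critical value in the 6.4 formula, whereas the alternative in section 4 is written as one-sided;
- the matching clustered model for the binary outcomes (anaemia, respiratory infection, diarrhoea).

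State how baseline village means are formed where households came from a neighbouring village. Align the sentence in the Abstract with this text. If an analysis plan already contains such a model, a reference to it from 6.6 is enough.

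The cost is wording only. The data are already collected under the plan, the sample size is unchanged, and the models run in the planned software.
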